##### 4.4.1.1 Participants characteristics at inclusion

Baseline differences between the two groups in terms of socio-demographic factors (age, gender, educational level, laterality, smoking status) and clinical characteristics (depression severity, illness duration, episode duration, treatment, level of early life adversity) will be analyzed using independent samples *t-*tests and chi-squared tests or non parametric tests depending on the distribution of the data.

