## 3 Methods: assignment of intervention

### 3.1 Sequence generation

Patients will be randomly assigned (1:1) to receive either iTBS alone or iTBS combined with pleasant olfactory stimulation. Computer-generated random numbers using the Sealed Envelope platform (https://www.sealedenvelope.com) will be used to generate the allocation sequence. Block of 2, 4, and 6 will be used to stratified the randomization.

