##### 4.2.1.2 Early life adversity

Childhood trauma and maltreatment negatively affect rTMS-left DLPFC treatment outcome in patients with MDD (Hu et al., 2021). Therefore, the short form of the CTQ will be used, which includes 28 items, rated from 0 to 5 according to the occurrence of the event experienced. It allows to identify 5 different types of trauma: emotional neglect, physical neglect, emotional abuse, physical abuse, and sexual abuse. Subtotals can be calculated for each type of trauma to provide a nuanced understanding of the participant's childhood trauma experiences.

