### 4.4 Statistical methods

#### 4.4.1 Statistical methods for analyzing primary and secondary outcomes

Statistical analysis will be performed using R studio (Boston, USA, with the latest version at the time of the analysis) by an experimenter blinded to treatment allocation. The alpha threshold will be fixed at 0.05. Parametric tests will be performed only when the assumptions for their application are met, otherwise, non-parametric tests will be performed.

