##### 4.4.1.2 Clinical data analysis

The proportion of remissions and responses will be investigated using chi-squared tests or Fisher's exact test. Changes in scores of depression severity, anhedonia and olfactory capabilities over the study period within the two groups will be analyzed using a mixed 2-way repeated measures ANOVA (GROUP^*^TIME) or a generalized linear mixed model depending on the distribution of the data. Pearson correlations will be performed to examine the relationship between olfactory anhedonia and pre-treatment physical and social anhedonia, as well as the relationship between childhood trauma severity and response to treatment, the relationship between childhood trauma severity and anhedonia (physical, social, and olfactory), and the relationship between childhood trauma severity and depression severity. Type of medication and type of depression (unipolar vs. bipolar) will be included in the analysis. We did not expect differences in response between patients with unipolar and bipolar depression.

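### Childhood trauma, which the plan says worsens the outcome of this stimulation, is measured at week 0 but enters no between-arm outcome analysis; the baseline significance tests do not make up for that

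*Protocol article*

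**What the plan says.** Allocation is randomised: "Patients will be randomly assigned (1:1) to receive either iTBS alone or iTBS combined with pleasant olfactory stimulation" (section 3.1). Section 4.4.1.1 then plans tests between the arms on five socio-demographic variables ("Baseline differences between the two groups in terms of socio-demographic factors (age, gender, educational level, laterality, smoking status") and five others: "clinical characteristics (depression severity, illness duration, episode duration, treatment, level of early life adversity". These "will be analyzed using independent samples *t-*tests and chi-squared tests or non parametric tests depending on the distribution of the data". Section 4.4.1 sets the level: "The alpha threshold will be fixed at 0.05". Illness duration, episode duration and treatment do not apply to healthy volunteers, so the two groups must be the randomised arms.

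Section 4.2.1.2 gives the reason for collecting the CTQ: "Childhood trauma and maltreatment negatively affect rTMS-left DLPFC treatment outcome in patients with MDD". Table 1 schedules the CTQ for patients at week 0 only.

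In section 4.4.1.2, "The proportion of remissions and responses will be investigated using chi-squared tests or Fisher's exact test". Scale scores go into a GROUP by TIME repeated-measures ANOVA or a generalized linear mixed model. Type of medication and type of depression are the only further factors named for inclusion. Trauma appears in Pearson correlations, among them "the relationship between childhood trauma severity and response to treatment", and these do not compare the arms.

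**The concern.** By the plan's own account, trauma is prognostic for a treatment given in both arms, and it is measured before treatment in every patient. That makes it a natural covariate for the arm comparison. The plan instead adds depression type, for which it expects no difference in response, and leaves trauma out. The only between-arm use of trauma is a baseline significance test, which is a poor instrument here. Under correct randomisation its null hypothesis is true, so a significant result is a false alarm. A non-significant result does not show that the arms are balanced closely enough.

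At stake is some precision in the scale outcomes, and protection against a chance trauma imbalance that would otherwise stay inside the estimated treatment effect.

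**Working it through.** The plan gives no figure on this point to reproduce.

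**Inputs.** 40 patients per arm and 30% remission with iTBS alone (section 2.6.1); alpha 0.05 (section 4.4.1); ten baseline variables, 5 + 5 (section 4.4.1.1). The documents give only a direction for the effect of trauma, so the correlation r between CTQ and the (latent) outcome is assumed to lie between 0.2 and 0.4.

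**Baseline tests.** The chance of at least one p < 0.05 by chance alone, if the ten tests are independent, is 1 − 0.95^10 = 0.401. The expected number is 10 × 0.05 = 0.5.

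**What a non-significant test allows.** The standardised baseline difference has SD sqrt(2/40) = 0.224. Significance needs a difference of about 1.96 × 0.224 = 0.44 SD. The chance of an imbalance above 0.3 SD is P(|Z| > 0.3/0.224) = 0.18.

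**Shift in the remission difference.** An imbalance of d SD moves the latent outcome by r × d. Near 30% remission, the normal density at the cut point is 0.348, so the shift is about 0.348 × r × d:

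| Imbalance d | r = 0.2 | r = 0.3 | r = 0.4 |
|---|---|---|---|
| 0.30 SD | 2.1 points | 3.1 points | 4.2 points |
| 0.43 SD | 3.0 points | 4.5 points | 6.0 points |

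For comparison, the standard error of the remission difference is sqrt(2 × 0.3 × 0.7/40) = 0.102, or about 10 points, and the planned effect is 60 − 30 = 30 points.

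**Conditional error for a continuous outcome.** Given a trauma imbalance of z standard errors, the unadjusted statistic has mean r × z and variance 1 − r² under no treatment effect. At z = 1.9, just short of significance, a nominal 5% two-sided test rejects in 6.2% (r = 0.2), 7.7% (r = 0.3) or 9.7% (r = 0.4) of such trials. Averaged over all possible imbalances, the rate is 5%.

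**Precision.** In a single-timepoint comparison, adjustment cuts residual variance by r²: 0.2² = 4% to 0.4² = 16%.

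**Which model term does the work.** In a GROUP by TIME model the treatment effect is the difference between arms in change from baseline. A CTQ main effect adds the same amount at every visit, so with complete data it cancels from each patient's change. In one simulated trial (40 per arm, four visits, an imbalance in trauma, trauma acting on post-baseline scores only), the GROUP by TIME estimate was:

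- without CTQ: 0.526 (SE 0.310);
- with a CTQ main effect: 0.526 (SE 0.310);
- with CTQ by TIME added: 0.370 (SE 0.303).

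Only the last adjusts the contrast of interest.

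**The case against.** Covariate lists are commonly settled in a statistical analysis plan, which is not shown here, and an unadjusted comparison of randomised arms is valid. The possible shift rests on an assumed correlation and is below one standard error. Chance imbalance of this kind is already covered by the test's type I error and the confidence interval. The primary outcome has no model to hold a covariate, because the sample size and the analysis both rest on a chi-squared test.

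Most of this stands, and it limits the point to an improvement. The objection about the analysis plan is weaker. Section 4.4.1.2 does name the factors to be included, and omits the one that section 4.2.1.2 calls prognostic, so the comment is on a stated choice.

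A reader might infer that the baseline tests will decide which covariates are used. Section 4.4.1.1 gives them no such role, so a false alarm there alters no outcome analysis, and a trauma imbalance would have the same effect if the tests were deleted. A reader might also take section 2.4.2, which lists the CTQ among outcomes compared between the groups, as covering the gap. With the CTQ scheduled only at week 0, that would be one more baseline comparison and no adjustment.

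**Conclusion.** The point holds as a modest improvement to the between-arm analyses. The plan calls trauma prognostic, measures it at week 0 and leaves it out of every comparison of the arms. The price is some precision, and a possible shift of about 2 to 6 points in the remission difference when the imbalance is 0.3 to 0.43 SD. This assumes r between 0.2 and 0.4, a latent-normal outcome and 30% remission.

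It would be tempting to conclude that the primary test is biased or invalid. The documents do not support that: allocation is randomised 1:1, and the unadjusted test keeps its error rate on average. The baseline p-values are a matter of presentation. The 40% false-alarm figure assumes independent tests, and no efficacy result depends on them.

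**What to change.** In section 4.4.1.2, prespecify the week-0 CTQ total as a covariate whatever imbalance is observed:

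- **Scale scores:** include CTQ and CTQ by TIME in the repeated-measures models, or compare post-treatment scores adjusted for the baseline score and CTQ. A CTQ main effect alone is not enough in the GROUP by TIME model.
- **Remission and response:** keep the chi-squared or Fisher test as the stated comparison. Beside it, add a CTQ-adjusted logistic regression, reported as a standardised risk difference, as a prespecified supporting analysis.

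In section 4.4.1.1, describe baseline characteristics by arm as means with SD or as counts, without p-values.

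The cost is a few model parameters and one extra analysis. No new data are needed, and the sample size and primary test are unchanged. The choice should be fixed before unblinded results are seen, so that it cannot depend on them.

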##### 4.4.1.2 Clinical data analysis

The proportion of remissions and responses will be investigated using chi-squared tests or Fisher's exact test. Changes in scores of depression severity, anhedonia and olfactory capabilities over the study period within the two groups will be analyzed using a mixed 2-way repeated measures ANOVA (GROUP^*^TIME) or a generalized linear mixed model depending on the distribution of the data. Pearson correlations will be performed to examine the relationship between olfactory anhedonia and pre-treatment physical and social anhedonia, as well as the relationship between childhood trauma severity and response to treatment, the relationship between childhood trauma severity and anhedonia (physical, social, and olfactory), and the relationship between childhood trauma severity and depression severity. Type of medication and type of depression (unipolar vs. bipolar) will be included in the analysis. We did not expect differences in response between patients with unipolar and bipolar depression.

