### 2.2 Eligibility criteria

#### 2.2.1 Patients with MDD

To be eligible for the study, patients must meet the following criteria: be 18 years or older, have a primary diagnosis of single or recurrent non-psychotic major depressive disorder (unipolar or bipolar) episode according to the Diagnostic and Statistical Manual of Mental Disorders, fifth edition (DSM-5) criteria, scored 20 or more on the 10-item Montgomery and Asberg Depressive Rating Scale (MADRS) (Montgomery and Åsberg, 1979) and scored higher than 2 on the MADRS anhedonia score (item #8). All patients should be able to speak and read French, and sign a written informed consent.

Patients with unipolar depression should be on stable antidepressant medication for at least 4 weeks prior to inclusion with no mood changes (after at least one previous treatment failure). Patients recruited for this study had a treatment-resistant depressive episode, defined as failure to respond to at least two antidepressant regimens despite adequate dosage, duration and adherence to treatment (McIntyre et al., 2023). Patients will remain on the same stable antidepressant medication throughout the trial without any changes. Benzodiazepines are not allowed.

Patients with bipolar depression should have treatment-resistant bipolar depression at enrolment, despite optimized mood-stabilizing treatment of adequate duration and dosage (for at least one month). Throughout the study period, patients will be on stable mono- or bi- therapy with mood stabilizers, without antidepressants or benzodiazepines (Bulteau et al., 2019).

Augmentation strategy with antipsychotics is allowed.

Participants will be not eligible if they have: anosmia [as verified by the European Test of Olfactory Capabilities (ETOC) (Thomas-Danguin et al., 2003)], whether congenital, or due to upper respiratory tract infection, nasal and/or sinus disease, brain injury or nasal surgery; neurological disorders; concurrent comorbid psychiatric disorders or substance abuse (except tobacco); contraindications to TMS (implanted medical devices or metallic foreign body in the head); contraindications to MRI; history of non-response to treatments based on sensory stimulation or rTMS; pregnant or breastfeeding mothers (controlled by urine pregnancy tests); a conservatorship or guardianship order.

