### 2.4 Outcomes

#### 2.4.1 Primary outcome

The primary outcome is the number of patients meeting remission criteria within each post-treatment group. Remission is defined as a MADRS score of 10 or less (Zimmerman et al., 2004) on a scale of 0–60, assessed at the end of 50 iTBS sessions.

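### The remission test makes no use of baseline MADRS, and the plan does not say whether its two named covariates apply to that test

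*Protocol article*

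**What the plan says.** All references are to the protocol article.

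- **Test.** Section 4.4.1.2: "The proportion of remissions and responses will be investigated using chi-squared tests" or Fisher's exact test. Section 2.6.1 sizes the trial on a chi-squared test as well.
- **Endpoint.** Section 2.4.1: "Remission is defined as a MADRS score of 10 or less", assessed after the 50 sessions. Section 2.2.1 requires an entry MADRS of at least 20, on a scale that runs to 60.
- **Baseline MADRS.** Table 1 schedules it at week -1 and week 0. Section 4.4.1.1 uses depression severity only to compare the groups at inclusion. No adjustment of remission for it is named.
- **Covariates.** Later in section 4.4.1.2: "Type of medication and type of depression (unipolar vs. bipolar) will be included in the analysis". No endpoint and no model is attached to this sentence. The models in that section that could take covariates (repeated measures ANOVA, generalized linear mixed model) are assigned to changes in scores, not to remission.
- **Medication by type of depression.** Section 2.2.1: "Patients with unipolar depression should be on stable antidepressant medication"; for bipolar depression, "patients will be on stable mono- or bi- therapy with mood stabilizers, without antidepressants or benzodiazepines". Antipsychotic augmentation is allowed without restriction by type.

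**The concern.** Remission here is a fixed threshold. A patient entering at 20 needs a much smaller drop to reach 10 than one entering at 40, so baseline severity is the obvious prognostic variable for this endpoint. It is collected, but the primary comparison ignores it. In a trial of 80 patients that is information given away.

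The covariate sentence adds uncertainty. If it is meant for remission, the named test cannot carry it out and the model is missing. If it is meant only for the score models, the text should say so. The remission result also decides early stopping at 0.005 and the final conclusion at 0.048 (section 5.1.2), so it should be fixed beforehand whether that p-value is adjusted. Finally, the two covariates may be one variable under two names, depending on how medication is coded.

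**Working it through.** **1. Starting power.** Inputs from section 2.6.1: 30% versus 60%, alpha 5%, power 80%, 37 per group, arcsine approximation.

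- h = 2·asin(√0.6) − 2·asin(√0.3) = 1.772 − 1.159 = 0.613.
- Two-sided n per group = 2·((1.960 + 0.842)/0.613)² = 41.8, so 42 and not 37. The one-sided formula gives 33. The stated 37 therefore does not reproduce. That is a separate matter, needed here only to fix the starting point.
- Power at 37 per group by the same formula: Φ(0.613·√18.5 − 1.960) = Φ(0.676) = 75%.
- Exact power of the uncorrected two-sided chi-squared test: 74.2%, the same at 0.05 and 0.048.

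**2. What baseline MADRS could add.** The protocol gives no correlation r between baseline and post-treatment MADRS, so r is varied. Model: latent score L = r·x + √(1 − r²)·e, with x the standardised baseline and e standard normal. A patient remits if L falls below Φ⁻¹(0.3) in the control arm or Φ⁻¹(0.6) in the combination arm. The adjusted test is a logistic regression on arm, baseline and depression type, with a likelihood-ratio test of arm. Setting: 37 per arm, alpha 0.048, 6,000 trials per cell (Monte Carlo standard error √(0.75·0.25/6000), about 0.6 points).

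| Assumed r | Chi-squared | Adjusted, likelihood ratio | Difference |
|---|---|---|---|
| 0 | 74.5% | 75.1% | 0.6 |
| 0.3 | 73.9% | 77.2% | 3.3 |
| 0.4 | 74.6% | 78.9% | 4.3 |
| 0.5 | 75.1% | 81.9% | 6.8 |

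With a Wald test of the arm coefficient, adjusted power is about 76% to 80% for r from 0.3 to 0.5. The range of gain is therefore about 2 points (76 − 74, Wald, r = 0.3) to about 8 points (81.9 − 74.2, likelihood ratio, r = 0.5).

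A second model, with an assumed baseline odds ratio per standard deviation and alpha 0.05 (4,000 trials per cell), agrees in pattern. For odds ratios of 1, 1.5, 2 and 3, likelihood-ratio power is 75.8%, 76.0%, 80.0% and 83.6%, against 75.1%, 73.8%, 74.9% and 74.5% for chi-squared. The gains are about 1, 2, 5 and 9 points.

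**3. Error rate.** Under no difference at nominal 4.8%, chi-squared rejected in 4.4% to 5.5% of trials and the adjusted likelihood-ratio test in 5.2% to 6.1%. A model-based risk-difference test is liberal to a similar degree, about 5% to 6%. The Wald test of the arm coefficient held its level. Part of the likelihood-ratio gain is therefore liberality, as the 0.6 points at r = 0 suggest.

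**4. Whether the two covariates are distinct.** Under section 2.2.1 every unipolar patient takes an antidepressant and no bipolar patient does.

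- Medication as antidepressant yes/no: antidepressant = 1 − bipolar. The columns intercept, arm, bipolar and antidepressant have rank 3 of 4.
- Three antidepressant classes with mood stabilizer as reference: the three indicators sum to 1 − bipolar, so rank is 5 of 6.
- Antipsychotic augmentation yes/no: rank 4 of 4, no duplication.

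In the first two cases one column is redundant. Dropping it leaves the arm effect estimable and unchanged.

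**The case against.** The strongest reply is that the plan is coherent and the rest is preference. Sections 2.6.1 and 4.4.1.2 agree on a chi-squared test, an unadjusted comparison in a 1:1 randomised trial keeps its level, and covariate coding is commonly left to a statistical analysis plan that is not shown. Most of this stands. Omitting baseline MADRS costs efficiency, not validity, and the size of the loss rests on a correlation that the documents do not give. The replacement test also has to be chosen with care, since the common likelihood-ratio version is slightly liberal.

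Four stronger readings are tempting and are not supported:

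- *That the primary analysis contradicts itself.* The covariate sentence is not tied to remission. It follows the sentences on score models and correlations, and could apply to those. It is an ambiguity.
- *That the two covariates are collinear as planned.* Duplication depends on a coding that is not given; antipsychotic augmentation would add separate information.
- *That an adjusted analysis would be unstable.* Even with exact duplication the arm effect stays estimable, so this does not follow.
- *That the randomisation is deficient because section 3.1 names no stratification factor.* Unstratified randomisation is valid. With an assumed 20 bipolar patients among 80, a split of 14:6 or worse has probability 0.069, which is ordinary chance imbalance. The protocol also expects no difference in response by type of depression.

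**Conclusion.** The point holds as a modest and cheap improvement, together with one wording gap to close. The unadjusted remission test is valid but forgoes about 2 to 8 points of power at 37 per arm. This assumes 30% versus 60% remission, a two-sided test at 0.048, and a baseline-to-post correlation of 0.3 to 0.5. If the correlation is near 0, almost nothing is lost. With a test that holds its level, the gain is nearer 2 to 6 points (76% to 80% against 74%).

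Separately, section 4.4.1.2 leaves open whether medication type and depression type apply to remission. One natural coding of medication would fully duplicate depression type under section 2.2.1, without harming the estimate of the arm effect.

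**What to change.** Before the interim look, name one primary analysis in section 4.4.1.2:

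- Logistic regression of week-2 remission on arm, week-0 MADRS (continuous) and depression type, reported as a standardised risk difference with its confidence interval. Name week 0, because MADRS is also scored at week -1.
- Name the test that yields the p-value, and choose one that holds its level: the Wald test of the arm coefficient, or a small-sample or permutation version. Check it at the interim setting too. With 20 per arm, the planning rates give only 20·0.3 + 20·0.6 = 18 remissions, and the boundary is 0.005; the error rates above are for 37 per arm at 0.048.
- Keep the unadjusted chi-squared test as sensitivity analysis.
- Drop medication type, or code it as antipsychotic augmentation yes/no. State which analyses the covariate sentence covers.

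If the sponsor prefers the unadjusted test, the minimum is to say that the remission test is unadjusted and that the covariates belong to the other analyses.

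The cost is analysis wording: all the variables are already collected. Two small downsides should be stated. The conditional odds ratio differs from the crude one, hence the standardised risk difference. The likelihood-ratio and model-based risk-difference tests run slightly liberal at this size, about 5% to 6% at nominal 4.8%.

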## 1 Introduction

### 1.1 Background and rationale

#### 1.1.1 Major depressive disorder and anhedonia

Major depressive disorder (MDD) stands as the most common psychiatric disorder, affecting 4.4% of the world's population (World Health Organization, 2017). Among the clinical manifestations, anhedonia, the inability to experience pleasure, is one of the core symptoms of depression, affecting 70% of patients with MDD and linked to increased suicide risk. Furthermore, it is typically resistant to the first-line treatment (Kelly et al., 2022), making it one of the priorities of mental health research (Ducasse et al., 2021). This symptom appears to be rooted in a dysfunction of the reward system, i.e., hyperactivity in the prefrontal cortex (PFC) and hypoactivity in the ventral striatum (Gorwood, 2008), in which dopamine (DA) plays a key role. Furthermore, the symptom of motivational anhedonia has been linked to an abnormal availability of DA receptors in the ventral striatum (Peciña et al., 2017). Importantly, anhedonia can be physical and social, but it can also affect the senses, including olfaction.

Olfactory anhedonia has been shown to contribute to disrupted eating, social interactions, and mood (Clepce et al., 2010). Interestingly, the reward system, impaired in anhedonia, is closely connected to the olfactory system through the olfactory tubercle located in the ventral striatum, directly linked to the ventral tegmental area (Ikemoto, 2007). Olfactory stimulation has even been shown to activate DA neurons within the reward circuits in mice (Midroit et al., 2021) and brain regions of the mesocorticolimbic pathway in humans (Rolls et al., 2003).

Furthermore, several studies have shown that odors can improve mood and feeling of calm (Canbeyli, 2022), and that improved olfactory capabilities are associated with a reduction in depressive symptoms (Sabiniewicz et al., 2022) in participants without psychiatric disorders. While these findings are encouraging, the impact of such olfactory interventions in patients with MDD remains unclear.

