##### 1.2.2.4 Olfactory anhedonia

Finally, our last objective will be to better characterize olfactory anhedonia (i.e., the impaired olfactory perception of pleasant odorants) by investigating its association with physical and social anhedonia, but also with early trauma. Olfactory anhedonia will be assessed before, immediately after treatment, after 1-month and 3-month follow-up through specific testing.

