#### 2.4.4 Olfactory anhedonia

Olfactory anhedonia will be assessed using an olfactory test in which the hedonic value of odorants will be evaluated before and after the treatment, as well as at 1 and 3 months after the treatment, and compared between the two groups. The relationship between olfactory anhedonia and physical and social anhedonia will be investigated, as well as its association with early life adversity.

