##### 4.2.1.5 Olfactory capabilities

The European Test of Olfactory Capabilities (ETOC) will be used to assess the ability to identify and detect odorants. This test involves the presentation of 16 odorants at supraliminal concentrations. In each trial, 4 tubes are presented to the participants, only one of which contains the odorant. The aim of the task is to identify the tube containing the odorant, followed by identifying the specific odorant from a set of 4 propositions. Both tests are scored out of 16.

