##### 4.2.1.6 Olfactory anhedonia

In addition, an olfactory hedonic judgment test will be assessed. It consists of the presentation of 20 odorants (with different hedonic value, from pleasant to unpleasant), 15 of which are monomolecular at a concentration of 20 Pa: isoamyl acetate, 2-phenylethanol, benzaldehyde, L-carvone, linalool, trans-anethol, benzyl-acetate, eucalyptol, cis-3-hexanol, citronellol, D-limonene, eugenol, n-caproic acid, trimethylamine, butyric acid, thioglycolic acid, and 5 are blended odorants: lemon/sweet orange/rosemary/bergamot/bitter orange/tree leaf/lavender/clary sage, linalool/d-limonene/linalyl acetate/beta-caryophyllene/beta-pinene/citral/geraniol/alphapinene/ eucalyptol/l-beta-bisabolene/menthone/geranyl acetate/2,6-dimethyl-5-heptenal/terpinolene, sweet orange/lavender/rosemary/bergamot/basil, vanilla extract/orange/ylang-ylang, and ylang-ylang/palmarosa/sweet orange/isoeugenol.

Participants will be allowed to freely smell each odorant presented in a randomized order. Then, participants will be asked to rate each odorant in terms of liking (“Is the smell pleasant?”), wanting (“Do you want to smell it again?”), intensity (“Is the smell intense?”), familiarity (“Is the smell familiar?”) (Chalençon et al., 2022). Each odorant will be rated on an analog scale ranging from 1 to 9 (1 for “Not at all,” 5 for “Neutral,” and 9 for “Extremely”).

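### Baseline correlations of olfactory anhedonia with physical and social anhedonia ignore graded smell ability, so partial loss of smell can induce a correlation, most plausibly with the Physical Anhedonia Scale

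*Protocol article*

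**What the plan says.** **Construct.** Section 1.2.2.4 glosses olfactory anhedonia as follows: "i.e., the impaired olfactory perception of pleasant odorants". The aim there is to study its association with physical and social anhedonia and with early trauma.

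**Measurement.** Section 2.4.4 says: "Olfactory anhedonia will be assessed using an olfactory test in which the hedonic value of odorants will be evaluated before and after the treatment". In section 4.2.1.6, "participants will be asked to rate each odorant in terms of liking", and also for wanting, intensity and familiarity, each from 1 to 9. No rule says which ratings, or which of the 20 odorants, form the score.

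**Smell function.** The patient exclusion in section 2.2.1 is anosmia checked by the ETOC. No criterion addresses partial loss. Section 4.2.1.5 describes an ETOC detection task and an ETOC identification task: "Both tests are scored out of 16". Table 1 places the ETOC, the hedonic test and the Chapman scales at week 0 for patients.

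**Analysis.** Section 4.4.1.2 sets the olfactory correlations: "Pearson correlations will be performed to examine the relationship between olfactory anhedonia and pre-treatment physical and social anhedonia". It adds Pearson correlations of childhood trauma with the three kinds of anhedonia. The variables it says will enter the analysis are medication type and depression type. Olfactory capabilities appear there only as an outcome followed over time.

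**The concern.** A patient may rate a pleasant odorant low because it is smelled but not enjoyed, or because it is hardly smelled at all. With only anosmia excluded, both kinds of patient are in the sample. Section 4.2.1.3 lists smell and food among the pleasures that the PAS asks about. Reduced smell can thus lower the odorant ratings and raise the PAS score in the same patient, even if the capacity for pleasure is intact.

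An unadjusted correlation cannot tell this apart from a true link between kinds of anhedonia. The secondary objective in section 1.2.2.4 is to characterise olfactory anhedonia through such associations, so a shared dependence on smell ability could be reported as a finding about pleasure. The variable that would help to separate the two is already collected.

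**Working it through.** The protocol gives no figure for this point, so there is none to reproduce. The check has two parts.

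**1. Is the route open in the text?**
- Entry: section 2.2.1 excludes anosmia only, so graded variation in smell remains.
- Route to the olfactory score: sections 2.4.4 and 4.2.1.6 take hedonic ratings of odorants that must first be perceived.
- Route to the PAS: section 4.2.1.3 includes smell and food in its content. The share of the 61 items concerned is not given.
- Route to the SAS: the same section describes pleasure from social and interpersonal experience. Nothing there depends on smell.
- Block: section 4.4.1.2 names two variables for inclusion, and neither is the ETOC score.

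The route is open for the PAS and only conjectural for the SAS.

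**2. How large could the induced correlation be?**

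Inputs:
- n = 80 patients (section 2.6.1). Healthy volunteers do not add to this, because Table 1 gives them no Chapman scales. Section 4.4.2 restricts analysis to patients with at least one post-treatment evaluation. With 7% attrition that is 80 × 0.93 ≈ 74, so n = 74 is shown too.
- Alpha = 0.05 (section 4.4.1), taken as two-sided; the protocol does not state the side.
- a = correlation of smell ability with the olfactory anhedonia score; b = its correlation with the other anhedonia score. The protocol gives neither. Both are **assumed** to lie between 0.2 and 0.5, with both scores oriented the same way.
- No direct link between the two anhedonia scores.

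Formulas:
- Induced Pearson correlation: r = a × b.
- Chance of p < 0.05 by Fisher z: d = atanh(r) × √(n − 3); P = 1 − Φ(1.96 − d) + Φ(−1.96 − d).

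Worked case, a = 0.4, b = 0.3, n = 80: r = 0.12; d = 0.1206 × √77 = 1.058; P = 1 − Φ(0.902) + Φ(−3.018) ≈ 0.185.

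| a | b | induced r | P at n = 80 | P at n = 74 |
|---|---|---|---|---|
| 0.2 | 0.2 | 0.04 | 6.4% | 6.3% |
| 0.3 | 0.3 | 0.09 | 12.4% | 11.8% |
| 0.4 | 0.3 | 0.12 | 18.5% | 17.4% |
| 0.4 | 0.4 | 0.16 | 29.4% | 27.5% |
| 0.5 | 0.5 | 0.25 | 61.1% | 57.6% |

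The smallest significant |r| is 0.220 at n = 80 and 0.229 at n = 74.

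**After adjustment.** The partial correlation given smell ability has numerator r − a × b. Under the no-direct-link assumption this is ab − ab = 0, and the false-positive rate returns to about 5%. That holds only if the ETOC captures smell ability without error. If the ETOC score correlates ρ with true ability, the numerator is ab(1 − ρ²), so some confounding remains.

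**The case against.** **Covariates for an exploratory correlation belong in the SAP, and the score itself is left open.** The second half stands. A reader might infer that olfactory anhedonia is the liking rating alone; the text says only hedonic value, and wanting could enter, or intensity could be used to condition the score. The first half stands in part. Section 4.4.1.2 does name the test and the variables to be included, and smell ability is not among them. A wanting score would face the same problem.

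**The correlations may not be strictly two-variable.** The sentence on medication and depression type follows them directly, and its scope is unclear. This is fair, but neither variable measures smell.

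**The introduction does not support the route.** A reader might take section 1.1.1, "improved olfactory capabilities are associated with a reduction in depressive symptoms", as evidence that smell ability confounds these correlations. It does not go that far. The sentence concerns participants without psychiatric disorders, the next one calls the impact of olfactory interventions in MDD unclear, and the outcome is depressive symptoms rather than anhedonia or trauma. The documentary support is the content of the PAS.

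**Perception may be part of the construct.** This stands. The gloss in section 1.2.2.4 speaks of impaired perception, so the documents do not support making an intensity-adjusted estimate the decisive one.

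**Childhood trauma is a different case.** This also stands. A reader might extend the point to the trauma correlations, but smell ability in adulthood cannot cause childhood trauma. It may lie on the path from trauma to olfactory anhedonia, and adjusting for it could then remove part of the association of interest.

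**The magnitude is assumed.** This is correct. The low end is practically nominal, and 61% needs both correlations at 0.5. Excluding anosmia also removes the extreme of the smell range.

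**Conclusion.** The point holds for the baseline correlation of olfactory anhedonia with the PAS, and less clearly for the SAS. Partial loss of smell can induce a correlation that the plan as written cannot distinguish from a link between kinds of anhedonia.

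The size is not known. The range of r from 0.04 to 0.25, significant in 6% to 61% of trials at n = 80, rests on assumed correlations of 0.2 to 0.5 and on no direct link; it is an illustration and not an estimate of this trial's false-positive rate. The documents do not show that the planned correlations will be spurious.

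Only a secondary objective is affected. The remission comparison and the treatment-effect analyses are untouched. This is an inexpensive improvement to the analysis.

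**What to change.** In section 4.4.1.2, for the baseline correlations of olfactory anhedonia with the PAS and the SAS:

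1. Report a partial correlation (or a linear regression) adjusted for the week-0 ETOC score beside the unadjusted Pearson correlation. State in advance which ETOC score is used, since detection and identification are scored separately.
2. Claim a link between kinds of anhedonia that is independent of smell ability only if the ETOC-adjusted estimate supports it.
3. Add the mean intensity rating of the same odorants as a further covariate in a sensitivity analysis only.
4. Keep the childhood-trauma correlation unadjusted for smell ability as its main estimate.

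Cost: a change of wording and one degree of freedom, with no new data or visits. The adjusted estimate may be somewhat conservative if weak smell is partly a feature of olfactory anhedonia, which is why both estimates are shown. Because the ETOC measures smell ability imperfectly, the adjusted estimate should be described as reducing this confounding, not removing it.
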